### Randomisation

#### Sequence generation

A computer-generated randomisation sequence with a block size of four will be generated using Stata (version 13 Stata Corp., College Station, TX, USA) and held by an independent biostatistician. A 1:1 randomisation ratio, with no stratification, will be used. Enrolled men will be randomised to one of the two arms of the study in equal proportions.

#### Allocation concealment mechanism

The biostatistician will provide the computerised randomisation sequence, containing the name of the mouthwash brand and a study identification number (ID) to two independent staff members at the Melbourne Sexual Health Centre. The two staff members at the Melbourne Sexual Health Centre will have the responsibility for preparing the mouthwash solutions according to the generated randomisation sequence. They will then replace the names of the mouthwash brands with ‘Study mouthwash A’ or ‘Study mouthwash B’ on a new list and provide this list to the principal investigator at each participating site. Only the biostatistician and the two staff members at the Melbourne Sexual Health Centre (who are not the OMEGA study investigators) hold the document containing the code connecting to the real name of the two commercial mouthwashes. Study ID allocation to consenting participants will proceed from the first study number in the randomisation sequence.

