**Methods/design:**

The OMEGA (Oral Mouthwash use to Eradicate GonorrhoeA) study is a double-blind RCT and will be conducted at several sexual health clinics and high caseload General Practice (GP) clinics in Melbourne and Sydney, Australia. A total of 504 MSM attending the participating sites will be recruited. Participants will be randomised to either using ‘Study mouthwash A’ or ‘Study mouthwash B’ for 12 weeks. Study mouthwash A was inhibitory against *N. gonorrhoeae* in vitro, whereas study mouthwash B was not. Participants will be instructed to rinse and gargle the study mouthwash for 60 seconds every day. The primary outcome is the proportion of participants with oropharyngeal gonorrhoea detected by nucleic acid amplification test by 12 weeks.

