### Intervention

Participants will be randomly allocated to one of two mouthwash solutions. Both are alcohol free commercial mouthwash products that are widely available in supermarkets and pharmacies in Australia – one is commercially advertised to be antibacterial (mouthwash A) and the other is not (mouthwash B). In our in-vitro study, we found that mouthwash A demonstrated an inhibitory effect against *N. gonorrhoeae* on culturing oropharyngeal swabs; this was not the case for mouthwash B.

Participants will receive a total of four study mouthwash bottles (2 × 500 mL bottles at baseline and 2 × 500 mL bottles at week 6) and will be asked to rinse and gargle 20 mL for 60 seconds at least once a day. Rinsing and gargling is important because our previous work has shown that gonorrhoea is detected at both the tonsillar fossae and the posterior oropharynx in MSM [89]. Figure 1 illustrates how to rinse and gargle a mouthwash, and this instruction sheet will be provided to all participants. A video clip is also available on the OMEGA study website for participants to review the procedure (www.mshc.org.au/omega). Participants can use the study mouthwash more than once a day but not more than five times a day. All participants will be required to stop using any other mouthwash they are currently using, during the study period.

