### Sample size

Sample size and power calculations were performed using Stata to compare two proportions (version 13 Stata Corp., College Station, TX, USA) [92, 93]. A previous study has shown that about 10% of MSM had a repeat culture positive for gonorrhoea within 12 weeks after a culture positive for gonorrhoea [88]. With NAAT is a more sensitive test and its detection rate five times higher compared to culture [56], we assumed oropharyngeal gonorrhoea positivity by NAAT in the arm using mouthwash B to be 20% over 12 weeks. Table 1 shows the number of participants required to detect a 50% reduction in oropharyngeal gonorrhoea positivity from 20% in the control arm to 10% in the intervention arm with 5% significance level and 80% and 90% power respectively. Calculations were also based on a 55% and 60% reduction in oropharyngeal gonorrhoea positivity. To detect a 50% reduction in oropharyngeal gonorrhoea positivity with 80% power, a total of 438 men will be required (i.e. 219 in each arm). This is a conservative effect size because our pilot data suggest that a single-dose of mouthwash is associated with a five-fold decrease in detection of gonorrhoea [86]. To allow for up to 15% loss of follow up [94], we will recruit a total of 504 men, 252 in each group. This will ensure 80% power to detect a 50% reduction in oropharyngeal gonorrhoea positivity from 20% to 10%, and 90% power to detect a 50% reduction from 25% to 12.5%.

**Table 1 Tab1:** Sample size calculations assuming 20% in the control arm will have a positive NAAT for oropharyngeal gonorrhoea within 12 weeks

Efficacy of mouthwash	Oropharyngeal gonorrhoea positivity in the intervention arm	Number of participants	
		80% Power	90% Power
50% reduction	10%	438	572
55% reduction	9%	356	464
60% reduction	8%	294	380

Calculations were based on 5% significance level

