### Blinding

The study investigators, research nurses and clinicians at each participating clinic, and the participants, are blinded after assignment to interventions. The study mouthwash will be repackaged and numbered at the Melbourne Sexual Health Centre and then sent to the participating clinics. As the two mouthwashes have different packing, colours and tastes according to their respective commercial production, we blinded the products by repacking both mouthwashes into identical containers where the two staff members at the Melbourne Sexual Health Centre will decant the commercial mouthwash into a 500 mL cleaned, opaque amber plastic bottle (Fig. 2). To blind the colour, one drop of food dye will be added to each repackaged bottle to ensure that the two mouthwashes have a similar colour which differs between the original mouthwashes. Since the taste is similar but not identical, we cannot guarantee participant blinding according to taste. However, it will be very unlikely that participants will be aware which mouthwash they use because there are around 70 different commercial mouthwashes available in Australia. The two mouthwash solutions have been tested among clinical staff at the Melbourne Sexual Health Centre and none could distinguish between the two solutions based on colour or taste. The repackaged bottle has a child-resistant cap and protected by a tamper-evident seal. All bottles will be labelled with the study ID in accordance to the randomisation sequence. All procedures (i.e. dispensing, adding food colouring, and sealing) will be performed under sterile conditions. The research nurse will ensure bottles have not been opened before dispensing.

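### The A/B list sent to each site's principal investigator lets that person foresee and decode allocations, which contradicts the stated blinding of investigators

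*Protocol article*

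**What the plan says.** Four parts of the protocol article bear on this.

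- **Allocation concealment mechanism.** The biostatistician gives two independent staff members a "computerised randomisation sequence, containing the name of the mouthwash brand and a study identification number (ID"). They swap the brand names for the letters A or B "on a new list and provide this list to the principal investigator at each participating site". The only thing expressly withheld from the investigators is the code from letter to brand. The section ends: "Study ID allocation to consenting participants will proceed from the first study number in the randomisation sequence".
- **What the letters mean.** The Abstract uses the same study labels and says that A inhibited the organism in vitro, "whereas study mouthwash B was not". The Intervention section repeats this: "one is commercially advertised to be antibacterial (mouthwash A) and the other is not (mouthwash B"). The Sample size section ties the letter to the control arm: "we assumed oropharyngeal gonorrhoea positivity by NAAT in the arm using mouthwash B to be 20% over 12 weeks".
- **Blinding.** "The study investigators, research nurses and clinicians at each participating clinic, and the participants, are blinded after assignment to interventions". Bottles are repackaged at one centre into identical opaque containers and labelled with the study ID.
- **Trial settings and Trial status.** There are five sites. A research nurse checks eligibility after referral by clinicians. Melbourne Sexual Health Centre has recruited since March 2016, and the other four sites were expected to open in June 2017.

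**The concern.** Allocation concealment means that nobody who can influence enrolment knows the next assignment. Blinding means that those named as blinded cannot tell which arm a participant is in. The described step gives an ordered list of IDs and arms to the person who leads each site, and the same document says which letter is active. Replacing the brand by a letter protects the commercial name. It does not protect the arm.

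Two things are at stake. First, a site leader who can see the next assignment could influence, knowingly or not, who is approached or enrolled and when. Second, the same person would know the arm of men already enrolled while taking part in decisions about the conduct and reporting of a trial described as double-blind. Even if neither happened, the report could not state without qualification that the site principal investigators were blinded.

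**Working it through.** No figure in the plan turns on this point, so the check is a reading of the sections side by side.

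1. **What is on the list.** The source sequence holds two items per entry: brand and study ID. The only change described is brand to letter. The new list therefore pairs each ID with A or B.
2. **Can the next assignment be foreseen?** IDs are issued in sequence from the first. If the last ID used was *k*, the next participant receives ID *k* + 1, and its letter can be read off the list. Without the list, under 1:1 allocation and with earlier arms masked, the chance of naming the next arm correctly is 1/2. With it, the chance is 1 for every ID listed.
3. **Can the letter be decoded?** Three sections answer this, and they agree:

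| Section | A | B |
|---|---|---|
| Abstract, Methods/design | inhibitory in vitro | not inhibitory |
| Intervention | marketed as antibacterial | not so marketed |
| Sample size | – | arm with the assumed 20% positivity, given in the same section as the control-arm rate |

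   The Abstract uses the same study label as the list, so the natural reading is that the letters correspond.
4. **Does withholding the brand code help?** No. Bias would come from knowing active versus control, and step 3 supplies that without any brand name.
5. **Comparison with Blinding.** Study investigators are declared blinded. A site principal investigator is a study investigator and, by steps 1 to 3, knows the arm of each listed ID. The two sections cannot both hold for that person.
6. **How many allocations are exposed?** The article does not say whether each site gets the whole sequence or only its own IDs.
   - Whole sequence: each of the five principal investigators could read all 504 planned allocations.
   - Own IDs only: each could read the allocations at the site concerned, and together the five lists cover the same 504.

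   Either way, the holder sees every upcoming allocation at their own site, which is what concealment is meant to prevent.
7. **Does a site need the list to dispense?** The bottles arrive already prepared and labelled by ID, so a nurse can dispense by ID alone. The article gives no purpose for the list at site level.

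**The case against.** **The breach is shown for one role only.** This stands. The research nurse checks eligibility, takes the oropharyngeal swabs, records extra bottles and measures returned volumes. Nothing says that nurses, clinicians or participants see the list, and the bottles are described as carrying IDs, not letters. A reader might infer that the whole trial is unconcealed and unblinded, or that swab collection and bottle replacement are compromised. The documents do not support that: those tasks belong to people who would learn the arm only if the list were passed on. The primary endpoint is also a laboratory NAAT result, and saliva and the non-standard-of-care study swabs are batch tested centrally.

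**The letters on the list might be coded independently of the published letters.** The intention to mask principal investigators is clear, since the brand code is held only by the biostatistician and two non-investigator staff. If the letters were scrambled, the holder would see groups but not arms. The article does not say so, and its identical labels point the other way. Even then, the group of the next man would be known in advance, and decoding one participant would decode everyone on the list. This softens the blinding point but does not rescue concealment.

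**A journal article condenses the full protocol.** True, but the problem is not an omission. The article affirmatively describes a step that undoes what the section heading promises.

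**The fixed block size.** A reader might add that the sequence, described as "A computer-generated randomisation sequence with a block size of four", makes allocation predictable in itself. Someone who knew every earlier arm in a block could be certain of position 4 always and of position 3 with probability 1/3, that is (1 + 1/3)/4 = 33% of allocations. That needs knowledge of earlier arms. Once the list is withheld those arms are masked, and while the list is held the block size is irrelevant. It is not part of this point.

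**Conclusion.** The point holds for the site principal investigators. As written, each can foresee and decode every allocation on the list received. That defeats concealment for that person and contradicts the statement that study investigators are blinded.

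The conclusion rests on three readings: the relabelled list keeps the study IDs, as its derivation implies; its letters match those in the Abstract, Intervention and Sample size sections; and the principal investigator has access to the protocol. If the second reading fails, concealment is still lost but knowledge of the arm is not established. Whether each list is complete or site-specific does not change the conclusion.

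The documents do not show that any nurse, clinician or participant is unblinded, or that selective enrolment occurred, and no size of bias in the treatment comparison can be derived from them. The contradiction should nevertheless be corrected before further sites open, because it touches a core claim of the design and is easy to remove.

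**What to change.** 1. Delete the step that sends the A/B list to the sites.
2. Supply sites only with bottles labelled by study ID, and a log of study IDs that carries no letter.
3. Keep the ID-to-arm list with the independent biostatistician and the two preparers, and provide code-breaks that open one ID at a time.
4. Where a list has already gone out, which may be the case at Melbourne Sexual Health Centre, retrieve it and document who held it and for how long.
5. In the trial report, qualify the concealment and blinding claims for any principal investigator who held a list, and state separately what is known about nurses, clinicians and participants.

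The cost is a protocol wording change, an instruction to the two preparers, individual code-breaks, and a short record for any site already supplied. It needs no extra participants, visits or tests, and no new randomisation sequence.

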### Blinding

The study investigators, research nurses and clinicians at each participating clinic, and the participants, are blinded after assignment to interventions. The study mouthwash will be repackaged and numbered at the Melbourne Sexual Health Centre and then sent to the participating clinics. As the two mouthwashes have different packing, colours and tastes according to their respective commercial production, we blinded the products by repacking both mouthwashes into identical containers where the two staff members at the Melbourne Sexual Health Centre will decant the commercial mouthwash into a 500 mL cleaned, opaque amber plastic bottle (Fig. 2). To blind the colour, one drop of food dye will be added to each repackaged bottle to ensure that the two mouthwashes have a similar colour which differs between the original mouthwashes. Since the taste is similar but not identical, we cannot guarantee participant blinding according to taste. However, it will be very unlikely that participants will be aware which mouthwash they use because there are around 70 different commercial mouthwashes available in Australia. The two mouthwash solutions have been tested among clinical staff at the Melbourne Sexual Health Centre and none could distinguish between the two solutions based on colour or taste. The repackaged bottle has a child-resistant cap and protected by a tamper-evident seal. All bottles will be labelled with the study ID in accordance to the randomisation sequence. All procedures (i.e. dispensing, adding food colouring, and sealing) will be performed under sterile conditions. The research nurse will ensure bottles have not been opened before dispensing.

**Fig. 2 Fig2:**
[figure not shown]
A photograph of the OMEGA mouthwash bottle for a participant, Study ID 001

### Trial schema

Figure 3 outlines the trial schema. This is a 12-week long trial which consists of one baseline clinic visit at week 0, and two follow-up visits at week 6 and week 12. Participants will also be required to return the home-based study pack by post at week 3 and week 9. A reminder SMS will be sent to the participants by the research nurse at each participating site 1 day before the clinic visit and the home-based study pack is due.

**Fig. 3 Fig3:**
[figure not shown]
Outline of OMEGA trial schema

#### Baseline

Participants will be asked to complete a questionnaire at the baseline visit will be conducted at the participating clinics.

#### Follow up

Participants will be followed up every 3 weeks during the 12-week trial which consists of two face-to-face clinic visits (at week 6 and 12) and two home-based specimen and data collection postal packs (at week 3 and 9).

The week 6 and week 12 follow up visits will be a face-to-face visit and will be conducted at the participating clinics. The follow up time points at week 3 and week 9 will consist of a questionnaire and home-based saliva collection, to be posted back to the Melbourne Sexual Health Centre. The home-based study pack will be disseminated to the participants at both baseline and week 6 clinic visits for week 3 and week 9 home-based study pack, respectively. The home-based study pack consists of: a questionnaire, a yellow cap specimen collection jar, an UriSwab (Copan Diagnostics, Brescia, Italy) for saliva collection, an instruction sheet for saliva collection (Fig. 4) and a prepaid padded postage bag addressed to the Melbourne Sexual Health Centre. All home-based study packs will be returned to the Melbourne Sexual Health Centre only for specimen processing, leaving all clinics to focus on recruitment and clinic visits.

**Fig. 4 Fig4:**
[figure not shown]
An instruction sheet illustrates the procedure for self-collection of saliva specimens

### Biospecimens collection and testing

Biospecimen collection varies depending on the study time point. Table 2 shows the schedule and biospecimens required at each time point.

**Table 2 Tab2:** Summary of study time and collection of specimens and data

Week	0	3	6	9	12
Location	Clinic	Home	Clinic	Home	Clinic
*A. Biospecimens*					
Oropharyngeal swab on both tonsillar fossae for gonorrhoea tested by NAAT			✓		✓
Oropharyngeal swab on posterior oropharynx for gonorrhoea tested by NAAT			✓		✓
Oropharyngeal swab on both tonsillar fossae for gonorrhoea tested by culture			✓		✓
Oropharyngeal swab on posterior oropharynx for gonorrhoea tested by culture			✓		✓
Oropharyngeal swab on both tonsillar fossae for gonorrhoea and chlamydia tested by NAAT					✓
Oropharyngeal swab on posterior oropharynx for gonorrhoea and chlamydia tested by NAAT					✓
Saliva for gonorrhoea tested by NAAT		✓	✓	✓	✓
First-void urine for gonorrhoea and chlamydia tested by NAAT					✓
Anorectal swab for gonorrhoea and chlamydia tested by NAAT					✓
Serology for HIV and syphilis^a^					✓
*B. Questionnaire data*					
Demographic characteristics (e.g. age, country of birth, education level)	✓				
History of mouthwash use (e.g. frequency, type of mouthwash)	✓				
Sexual risk behaviours	✓	✓	✓	✓	✓
Antibiotic use	✓	✓	✓	✓	✓
Mouthwash adherence		✓	✓	✓	✓
Adverse events		✓	✓	✓	✓
Mouthwash acceptability/tolerability					✓

*NAAT* Nucleic acid amplification test

^a^HIV-positive men will only be tested for syphilis but not HIV

#### Saliva

Participants will be required to self-collect a saliva sample every 3 weeks. Figure 4 illustrates how to self-collect a saliva sample. This instruction sheet will be given to the participants and a video clip is available on the OMEGA study website for participants to review the procedure (www.mshc.org.au/omega). In brief, participants will be instructed to accumulate saliva in the mouth for about 30 seconds to get a reasonable volume of saliva. Participants will spit as much saliva as possible into a yellow cap specimen collection jar, and saliva will be collected by using an UriSwab (Copan Diagnostics, Brescia, Italy). Saliva samples at week 6 and week 12 will be collected at the participating clinic under the research nurse’s supervision; while saliva samples at week 3 and week 9 will be collected at home by participants. All saliva specimens collected will be transported by using UriSwab.

All participants will be required to send their home-based collected UriSwabs to the Melbourne Sexual Health Centre at week 3 and 9 by post. The research nurse at each participating clinic will be required to send clinic-based collected UriSwabs to the Melbourne Sexual Health Centre at week 6 and 12 by post.

Once the research team at the Melbourne Sexual Health Centre receives the UriSwab by post, the UriSwab will be immediately centrifuged at 1200 g for 1 min to separate the saliva from the UriSwab sponge. The centrifuged saliva will be pipetted into a sterile 2.0 mL micro tube (Scientific Specialties, Inc., CA, USA) and stored at −80 °C freezer at the Melbourne Sexual Health Centre for testing.

All centrifuged saliva samples will be batch tested at the Royal Women’s Hospital, Molecular Microbiology Laboratory, Melbourne. The saliva samples will be placed on the MagNA Pure 96 Instrument (Roche Diagnostics, Mannheim, Germany) for DNA purification and will be assessed for sampling and extraction adequacy by amplifying a 260 bp region of the human beta-globin gene [95]. The gonococcal bacterial DNA load of the sample will be quantified using qPCR assays targeting the *N. gonorrhoeae opa* gene. All samples positive for the *opa* gene will then be confirmed using a qPCR targeting the *N. gonorrhoeae porA* gene [96, 97].

#### Oropharyngeal swabs

Pharyngeal specimens will be collected at week 6 and week 12 clinic visits. All oropharyngeal swabs will be collected by the research nurses at each participating site. All swabs will be taken by no more than two research nurses at each site to minimise the variability of sampling technique [98]. All research nurses at each site will be trained on how to take a oropharyngeal specimen for this study, and an instruction sheet and a video clip will be provided to the research nurses to review the procedure (Fig. 5).

